### Sleep disorder treatment

Based on the sleep diagnosis, a sleep treatment plan will be made by the multidisciplinary team described above. Furthermore, the treatment plan will be discussed with the participant’s mental health professional to ensure it fits with the patient’s overall treatment plan. Examples of standard sleep interventions are: psychotherapies, (e.g. CBT-I and IRT), chronotherapy (e.g. light and dark therapy), treatment for sleep related breathing disorders (e.g. continuous positive airway pressure (CPAP)) and/or medication)(overview provided in Table 1). All sleep disorder treatments are well established and follow international guidelines. Also, current treatments were evaluated by patient representatives from each mental disorder diagnostic group and by experienced practitioners of the sleep centre, prior to the start of the study. Where appropriate, treatments were adjusted to decrease the burden on the participants, to increase treatment compliance, and/or efficacy. Treatments will be delivered by trained psychologists and in case of medication use and/or advice a psychiatrist will be involved in the treatment as well.

**Table 1 Tab1:** *Overview of indicated sleep interventions*

Sleep disorder	Treatment options
**Insomnia**	CBT-I; lifestyle advise; adjustments of medication, treatment with medication
**OSAS**	Lifestyle advise; CPAP; positional trainer; mandibular repositioner appliance (MRA); adjustments of medication
**Delayed Sleep Phase Syndrome (DSPS)**	Lifestyle advise; chronotherapy; treatment with melatonin
**RLS/PLMD**	Lifestyle advise; adjustments of medication; treatment with medication
**Hypersomnia**	Daily scheduled nap; lifestyle advise; treatment with medication
**Nightmare disorder**	IRT; Eye Movement Desensitization and Reprocessing (EMDR); treatment with medication; medication advise

### Sample size calculations

Power analysis were performed using G*Power software [45]. Based on previous studies [18, 46], we aim at an effect size of 0.4 (Cohen’s d) for the outcome variables “quality of life”, “general functioning” and “mental disorder specific symptoms”. Power analysis based with an α of .05 and a power of .8, resulted in a required group size of 48 patients per diagnostic group (24 TAU+SI-T0 and 24 TAU+SI-T1). Due to limitations in recruitment capacity in less prevalent disorders, differences across both sexes will only be examined in the relatively high prevalent disorders: depression and PTSS. Power analysis with a 2 × 2 experimental group design (TAU+SI-T0 versus TAU+SI-T1; and males versus females) as between subject factors and the three time points as within subject factors suggests that with an α of .05 and a power of .8 a group size of 92 per group (46 TAU+SI-T0 and 46 TAU+SI-T1) would be sufficient. This analysis assumes an equal sex distribution. Overall, a total of 472 participants will be included in this study (overview provided in Table 2).

**Table 2 Tab2:** *Overview of targeted sample-sizes per diagnostic category*

Group	Prevalence (%)	Sec. analysis: yes/no	Required number per experimental group	Total required number per diagnostic subgroup	% of total population needed to include
**Depression**	17	Yes	46	92	15.0
**Bipolar disorder**	3	No	24	48	44.4
**Anxiety disorder**	10	No	24	48	13.3
**PTSD**	15	Yes	46	92	18.1
**ADHD/ADD**	9	No	24	48	14.7
**ASD**	4	No	24	48	33.1
**SSD**	5	No	24	48	26.7
**Personality disorder**	6	No	24	48	22.3
**Total**			**236**	**472**	

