#### Effect of sleep disorder treatment

Nearly all sleep disorders induce disturbed sleep and consequently result in a sleep deficit. We hypothesize that the sleep deficit, rather than the underlying disorder, may be most influential on the added burden of the sleep disorder on the patient’s mental well-being. Therefore, in the analysis of the effects of added sleep interventions, no distinction will be made between the different all types sleep disorders and all treatments will be lumped together. The effects of added sleep intervention in all participants with a sleep disorder will be assessed at six and twelve months by comparison of treatment (TAU-SI-T0 and TAU-SI-T1) groups over time (T0, T1, and T2). Secondary analysis will focus on the interaction between treatment effect and sex differences. For statistical evaluation linear mixed models, separate for all outcome parameters, will be employed. A stepwise approach will be followed in which first results for crude models will be taken, after which models including potential confounders such as age, sex, and social demographic parameters are run.

These analyses will be performed in the total population for the quality of life and general symptom outcome parameters, and in the eight mental disorder diagnostic subpopulations (depressive disorder, bipolar disorder, anxiety disorder, PTSD, AD(H)D, ASD, SSD and personality disorder) for the specific mental disorder symptom parameters. Due to power limitations, secondary analysis will only be performed within the more prevalent disorders: depression and PTSD.

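### 24 patients per arm do not give 80% power for d = 0.4 within a diagnostic group; the stated inputs need about 100 per arm, so the per-disorder power claim should be withdrawn and restated

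*Protocol article*

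**What the plan says.** Under Sample size calculations, the article says "we aim at an effect size of 0.4 (Cohen’s d"), and applies this "for the outcome variables “quality of life”, “general functioning” and “mental disorder specific symptoms". It continues: "Power analysis based with an α of .05 and a power of .8", which "resulted in a required group size of 48 patients per diagnostic group (24 TAU+SI-T0 and 24 TAU+SI-T1"). The software is named ("Power analysis were performed using G*Power software"). For this first calculation the test, its sidedness and the correlation between time points are not.

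A second calculation, for the sex-by-treatment question in depression and PTSD, concludes that "a group size of 92 per group (46 TAU+SI-T0 and 46 TAU+SI-T1) would be sufficient". Table 2 therefore has six groups of 48 and two of 92: 6 × 48 + 2 × 92 = 472, or 236 per arm.

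Under Effect of sleep disorder treatment, the outcomes are split: "These analyses will be performed in the total population for the quality of life and general symptom outcome parameters". The disorder-specific symptom scales are analysed within the eight diagnostic groups, by linear mixed models over T0, T1 and T2.

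**The concern.** Effect size, alpha, power and the resulting sample size are all printed, and the size does not follow from the other three. Twenty-four per arm is about a quarter of what a two-arm comparison at d = 0.4 requires.

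The groups concerned carry real weight. The Study outcomes section lists severity of specific mental disorder symptoms among the primary outcomes. The Discussion expects sleep treatment to help more in some disorders than in others, so results will be read disorder by disorder. If the trial is understood to have 80% power in each disorder, a non-significant result in one of them invites the conclusion that sleep treatment does not help there. At the power actually available, a non-significant result in any one of the 48-patient groups is more likely than not, at correlations up to 0.7, even if the assumed effect is real.

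**Working it through.** **Inputs from the article:** d = 0.4 (so SD = 1), alpha .05, power .8; 24 per arm in six groups, 46 per arm in two, 236 per arm pooled; three time points.

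**Assumptions:** two-sided test as base case (one-sided also shown); correlation ρ between baseline and follow-up of 0.5 to 0.7.

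**1. Size needed for d = 0.4.** Normal approximation: n per arm = 2(1.960 + 0.842)²/0.4² = 2 × 7.85/0.16 = 98.1, so 99. The exact noncentral t gives 100 per arm, or 78 one-sided. The stated 24 is not reproduced.

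**2. Power with 24 per arm.** Noncentrality = 0.4 × √(24/2) = 1.386 on 46 df, giving power of 27.4% two-sided and 39.0% one-sided.

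**3. Baseline adjustment.** The effective effect size is d/√(1 − ρ²): 0.4/0.866 = 0.462 at ρ = 0.5 and 0.4/0.714 = 0.560 at ρ = 0.7. The required sizes are 75 and 52 per arm. Without adjustment, 24 per arm detects d = 0.826 at 80% power. Reaching 80% at d = 0.4 therefore needs √(1 − ρ²) = 0.4/0.826 = 0.484, so ρ is about 0.875.

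| Per arm | Power for d = 0.4: unadjusted / ρ 0.5 / ρ 0.7 | d detectable at 80%: unadjusted / ρ 0.5 / ρ 0.7 |
|---|---|---|
| 24 | 27% / 35% / 48% | 0.83 / 0.72 / 0.59 |
| 46 | 48% / 59% / 76% | 0.59 / 0.51 / 0.42 |
| 236 (pooled) | 99% unadjusted | 2.802 × √(2/236) = 0.26 unadjusted |

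**4. Can a repeated-measures routine give 48?** For the group-by-time interaction, the noncentrality is λ = f²·N·m/(1 − ρ), with m = 3 time points.
- Entering f = d/2 = 0.2 gives N = 58, 50 and 42 at ρ = 0.3, 0.4 and 0.5. At ρ = 0.42, N = 48 has 79.9% power.
- A 0.4 SD difference that first appears at T1 does not correspond to f = 0.2. For arm differences of (0, 0.4, 0) or (0, 0.4, 0.4), the SD across time points is 0.4 × √2/3 = 0.189, and f is half of that, 0.094. At N = 48 and ρ = 0.5, λ = 0.00889 × 48 × 3/0.5 = 2.56 and power is 27%; at ρ = 0.7 it is 43%. Reaching 80% takes 184 or 110 patients per diagnostic group.
- Conversely, f = 0.2 on this interaction means a T1 difference of 0.4 × 0.2/0.0943 = 0.85 SD.
- A between-arms repeated-measures test with f = 0.4, two time points and ρ = 0.8 also gives N = 48. With two arms, f = 0.4 is a difference of 0.8 SD.

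Both routes reach 48 by using an effect about twice the stated one.

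**5. Does one setting explain both stated sizes?** With f = 0.2 and ρ = 0.42, the four-group interaction at N = 92 has about 92% power, not 80%. So that setting does not account for both figures.

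**The case against.** The strongest reply is that the planned analysis is a linear mixed model over three time points, so a single-time-point t-test is too pessimistic. This is partly right. Averaging T1 and T2 with a fully sustained 0.4 SD difference and baseline adjustment gives about 48-62% at correlations of 0.5-0.7. That is still below 80%, and a sustained difference at T2 is doubtful because controls start the sleep intervention at T1. It also stands that the 35-48% range depends on correlations the article does not give, and that the 27% depends on a two-sided test. A journal article may leave the software settings to a fuller document, so their absence is not held against it. The objection is to printed inputs that do not lead to the printed size.

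A reader might infer three stronger things that the document does not support:

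- **That d was entered as f = 0.2.** This is one route to 48, but item 4 of the working shows another. The article does not say which setting was used.
- **That most of the eight disorder-specific comparisons will be null.** With six groups at 24 per arm and two at 46, the expected number of significant results if d = 0.4 everywhere is 6 × 0.274 + 2 × 0.475 = 2.6 unadjusted and 6 × 0.347 + 2 × 0.592 = 3.3 at ρ = 0.5. At ρ = 0.7 it is 6 × 0.476 + 2 × 0.757 = 4.4, which is more than half.
- **That quality of life and general functioning are underpowered because the per-group size is also claimed for them.** They are analysed pooled, at about 99% power for d = 0.4. The mismatch is one of wording and harms no inference.

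**Conclusion.** The power statement is wrong as written. At d = 0.4, 24 per arm gives about 27% power unadjusted and about 35-48% with baseline adjustment at assumed correlations of 0.5-0.7; only a correlation near 0.875 would rescue it. The 46 per arm in depression and PTSD also falls short of 80% for d = 0.4 over the same range. The error is confined to the disorder-specific symptom comparisons within the eight groups. It does not touch the pooled analyses, and it does not show that the trial as a whole is too small.

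These figures are before any loss. The enrolment total of 472 equals the sum of the calculated sizes, and the missing-data section removes some participants from the treatment part, so analysed numbers can only be lower. As an illustration, an assumed 20% loss leaves about 19 per arm and an unadjusted power of about 22%.

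The correction is needed because the claim is published and bears on primary outcomes, and because making it costs nothing in enrolment.

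**What to change.** Leave enrolment as it is and change the text:

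1. Withdraw the statement that 48 patients per diagnostic group give 80% power for d = 0.4.
2. State instead that a 48-patient group has 80% power only for d of about 0.6-0.8, and a 92-patient group only for d of about 0.4-0.6. Give the assumed correlation and the sidedness with these figures.
3. State that the pooled population (236 per arm) detects d of about 0.26 before any loss or multiplicity adjustment, and that this is the figure relevant to quality of life and general functioning.
4. Report disorder-specific effects as estimates with confidence intervals, and say in advance that a non-significant result in one disorder will not be read as absence of effect.

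The hierarchy of outcomes need not change. Whether to promote a pooled outcome to a confirmatory role is a separate decision that this correction does not require. The cost is rewording, and stated power that looks less favourable.

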### Statistical analyses

#### Data exploration/ missing data

Separate analyses will be performed for the different questionnaires, using SPSS (version 23) and R software. If data are not normally distributed, data transformations will be performed. A data management plan was generated using online software and can be found at DMPonline (https://dmponline.dcc.ac.uk/).

If a participant stops participation halfway the study or if a specific questionnaire is missing at a specific time point this will be dealt with as follows: if the last data point (T2) is missing, the participant will be included in the analysis for the prevalence and in any analysis focussed on de comparison between T0 and T1. For those participants that are missing a complete questionnaire at T1, but do have the T2 measurements, T1 will be treated as a missing data point and imputed using multiple imputation. If a participant is missing both the T1 and T2 data point, this participant will only be included in the prevalence analysis.

Because we make use of a delayed start for the sleep treatment in the TAU-SI-T1 group, there is a possibility that some participants in the TAU-SI-T1 control group score above the cut-off score for a sleep disorder on the HSDQ at T0, but below the cut-off score for a sleep disorder at T1. In this case, these participants will be informed about the change in their HSDQ score, and that they are no longer eligible for sleep disorder treatment, and thus excluded from the treatment part of the study. Another scenario is that a participant scores above a cut-off score of the HSDQ, but that the sleep disorder is not confirmed in the diagnostic evaluation. In this case, the participant will also be excluded from the treatment part of the study.

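### The missing-data rules appear to keep participants without T2 out of the twelve-month mixed-model comparison, which wastes observed data and can bias the T2 contrast

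*Protocol article*

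**What the plan says.** The Protocol article, under Data exploration/ missing data, sets three rules for an incomplete participant.

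- T2 missing: "if the last data point (T2) is missing, the participant will be included in the analysis for the prevalence and in any analysis focussed"; the analyses meant are those of T1 against T0.
- T1 missing, T2 present: "T1 will be treated as a missing data point and imputed using multiple imputation".
- Both missing: "If a participant is missing both the T1 and T2 data point, this participant will only be included in the prevalence analysis".

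Nothing is said about imputing T2. Under Effect of sleep disorder treatment, the efficacy analysis is set as follows: "For statistical evaluation linear mixed models, separate for all outcome parameters, will be employed". The effect of the added sleep intervention "will be assessed at six and twelve months by comparison of treatment (TAU-SI-T0 and TAU-SI-T1) groups over time (T0, T1, and T2").

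**The concern.** The rules do not fit the model. A linear mixed model fitted by likelihood takes whatever rows a participant has. It needs no imputed T1 for someone with T0 and T2, and it can use T0 and T1 from someone without T2. The rules instead fill in the first kind of participant and send the second kind to other analyses, which leaves people with T2 as the basis of the twelve-month comparison.

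Two consequences follow directly from that reading. Observed T0 and T1 scores are lost to the twelve-month analysis. And the six-month result includes people without T2 while the twelve-month result does not, so the two cannot be read as one course over time in the same patients.

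A third consequence is conditional. Neither researchers nor participants are blinded (Design). At T1 one arm has already been offered sleep treatment and the other is about to start it (Procedure). The T1 score may therefore relate to leaving in different ways in the two arms. If it does, those who reach T2 are no longer comparable by arm.

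**Working it through.** **Inputs from the Protocol article.** The target effect is stated as "we aim at an effect size of 0.4 (Cohen’s d"), with 24 per arm in most diagnostic groups (46 in depression and PTSD). The article gives no dropout rate, correlation between time points or dropout mechanism, so there is no figure of its own to reproduce on this point. Everything below that line is an assumption.

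**Assumed set-up.** Scores have SD 1, and higher is worse. Means at T0, T1, T2 are (0, 0, 0) in the delayed arm and (0, -0.4, 0) in the early arm, so the true T2 difference is 0. Dropout after T1 is logistic with slope 0.8, with opposite signs by arm: good scorers leave the delayed arm (19% lost) and poor scorers leave the early arm (15% lost). Dropout depends either on the T1 score or on the T1-T0 change. Correlations are either (A) 0.6 throughout, or (B) 0.6 for T0-T1, 0.7 for T1-T2 and 0.4 for T0-T2. The simulation used 1,000,000 per arm. The MAR estimate regresses T2 on T0 and T1 among completers within arm, then averages the prediction over everyone with T0 and T1.

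Bias in the early-minus-delayed contrast at T2 (SD units):

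| Dropout driven by | Correlations | Raw T2 | T2 adjusted for T0 | T0-T2 change | MAR estimate |
|---|---|---|---|---|---|
| T1 score | A | -0.15 | -0.06 | 0.00 | 0.00 |
| T1 score | B | -0.17 | -0.12 | -0.02 | 0.00 |
| T1-T0 change | A | 0.00 | -0.06 | -0.10 | 0.00 |
| T1-T0 change | B | -0.07 | -0.12 | -0.18 | 0.00 |

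**Check by formula, T1-driven dropout.** Let d be the shift that selection causes in the T1 difference among completers. The simulated T0 shift is -0.149, so d = -0.149/0.6 = -0.248. T0 shifts by r01 × d and T2 by r12 × d.

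- Change bias is (r12 - r01) × d: A gives 0; B gives 0.1 × -0.248 = -0.025.
- Raw bias is r12 × d: A gives 0.6 × -0.248 = -0.149; B gives 0.7 × -0.248 = -0.174.
- T0-adjusted bias is about (r12 - r02 × r01) × d: A gives 0.24 × -0.248 = -0.060; B gives 0.46 × -0.248 = -0.114.

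**Check by formula, change-driven dropout.** The variance of T1-T0 is 2 × (1 - 0.6) = 0.8. T0 shifts by (0.6 - 1)/0.8 = -0.5 times the shift in the T1-T0 difference. The simulated T0 shift is 0.101, so the shift in T1-T0 is -0.202. T2 shifts by (r12 - r02)/0.8 × -0.202: A gives 0; B gives 0.375 × -0.202 = -0.076. The change bias is then 0 - 0.101 = -0.10 for A and -0.076 - 0.101 = -0.18 for B.

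**When it disappears.** With completely random dropout all contrasts are unbiased. With the same slope in both arms, all contrasts are within about 0.02.

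**Heavier loss and the opposite direction.** Take a true T2 difference of -0.40, correlation 0.5, slope 1, and dropout driven by T1-T0 change with those doing worse leaving the delayed arm. The completer change contrast is then about -0.31, -0.27 and -0.23 at 20%, 30% and 40% loss. If those doing better also leave the early arm, it is about -0.23, -0.15 and -0.07. The MAR estimate stays at -0.40. Here the bias hides an effect, so its sign is not predictable in advance.

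**Information lost.** At 15% and 19%, a group with 24 per arm loses 0.15 × 24 = 3.6 and 0.19 × 24 = 4.6 participants from the twelve-month comparison, although their T0 and T1 scores are in hand.

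**The case against.** Three objections carry weight.

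First, exclusion from the mixed model is implied, not written. The rule for a missing T2 lists analyses that the participant enters; the restricting word appears only in the rule for missing both T1 and T2. The six-month contrast of the mixed model is itself a T0-T1 comparison, so entering these rows is compatible with the text. This stands as a caution on wording. The natural reading still goes the other way: such a list serves little purpose if the participant enters the main model anyway, and imputing T1 only when T2 exists suggests that complete sets of three were wanted.

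Second, a reader might infer that the twelve-month result is biased, by about 0.15 SD or more than a third of the 0.4 target. The document does not support that. The figure belongs to a raw T2 difference. The planned comparison of groups over time includes T0, and in the same scenario (T1-driven dropout, equal correlations) the change contrast is unbiased and the T0-adjusted bias is -0.06. Larger bias in those contrasts needs unequal correlations or change-driven dropout, which are also assumptions.

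Third, the reach is limited. The six-month comparison, where only one arm has had sleep treatment, keeps participants without T2. And if dropout depends on unobserved scores, the mixed model can be biased too.

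**Conclusion.** The point holds as a stated rule that undercuts the stated model. On the natural reading, two effects are certain once anyone misses T2 after giving T1: observed T0 and T1 data are lost to the twelve-month comparison, and the six- and twelve-month results describe different patients. Bias in the T2 contrast is possible, not established. Under the assumed 15-19% dropout in opposite directions by arm it lies between about 0 and 0.18 SD, against about 0 for the likelihood analysis under MAR. It is larger with heavier loss, absent under completely random dropout, and negligible when the mechanism is the same in both arms. The dropout rates, mechanisms and correlations are all assumptions. The six-month comparison is not affected.

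**What to change.** Replace the three rules with one statement: every randomised participant with T0 and at least one of T1 or T2 enters a single likelihood-based linear mixed model over T0, T1 and T2, with no imputation of whole questionnaires. If imputation is preferred, impute T2 as well as T1. A sensitivity analysis for departures from MAR is a useful option but not essential to the point; covariance structure and the handling of baseline can be left to the analysis plan. If the intention was always to enter participants without T2 in the model, one sentence saying so settles the matter.

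The cost is a change of wording. SPSS and R, already named in the article, fit this model, and no extra data or patients are needed.

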## Background

Sleep problems are among the most frequent complaints in individuals with a mental disorder. Therefore, sleep disorders are common in individuals with mental disorders. Chronic insomnia, for example, is estimated to affect more than 40% in schizophrenia spectrum disorders [1], compared to approximately 6% in the general population [2]. Furthermore, insomnia complaints were reported in more than 50% in individuals with an affective disorder [3]. Six categories of clinical sleep disorders are identified in the International Classification of Sleep disorders (ICSD-3); insomnia, sleep related breathing disorders (SRBD), central disorders of hypersomnolence (hypersomnia), circadian rhythm sleep-wake disorders (CRSD), parasomnias, and sleep-related movement disorders [4]. Although insomnia prevalence has been investigated in connection with several different mental disorders, prevalence rates for the other categories of sleep disorders have been less or not at all studied in connection to the presence of mental disorders. More detailed information on the prevalence of a certain sleep disorder in connection to particular mental disorders could improve treatment strategies and may even lead to the identification of novel etiological pathways underlying the respective sleep disorders.

Studies suggest that sleep disorders increase the risk for the development of mental disorders, and worsen treatment outcome [5–7]. For instance, insomnia has been shown to have prognostic validity for the development of posttraumatic stress disorder (PTSD) [6, 8] and depression [9, 10]. Moreover, the already high vulnerability for suicidal behavior in individuals with mental health problems is further increased in those with poor sleep [11, 12]. Thus, early and adequate treatment of sleep disorders in individuals with mental disorders may be of paramount importance, and might well lead to better mental health outcomes and improved quality of life.

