### Procedure

As part of the intake procedure of the mental health institute, routine outcome assessment (ROA) measurements are conducted in most departments of the institute, using an established online platform [21]. We will use this infrastructure, to reduce the burden to the participants and ensure data quality. Participants will be asked to complete questionnaires prior to the intake procedure (T0), 6 (T1), and 12 (T2) months later.

To screen for sleep disorders, patients fill out the Holland Sleep Disorders Questionnaire (HSDQ) [22, 23]. Patients who score above the cut-off score for any specific category of sleep disorders will be invited to participate in this study. After being informed about the study procedures, they will be asked for informed consent.

For both the experimental and control conditions, participants will continue their treatment as usual (TAU) throughout the study. After stratification for type of mental disorder, participants will be randomly assigned (using Sealed Envelope software) to either the experimental or control condition. In the experimental condition sleep intervention(s) (SI) will start immediately at T0 (TAU+SI-T0). In the control condition, the sleep intervention(s) will first start six months after inclusion, at T1 (TAU+SI-T1). This allows to test the effects of early interventions for sleep disorders on mental disorder symptoms, general functioning, sleep, and quality of life. Sleep interventions generally start with extensive diagnostic evaluation, followed by patient-targeted sleep treatment. For individuals scoring below the cut-off score for a sleep disorder on the HSDQ, participation is limited to filling out the questionnaires at T0. An exception to randomised allocation will be made for participants in the control condition whose HSDQ result or intake interview indicates a very severe sleep disorder, such as Narcolepsy. These participants will be immediately referred to a sleep centre, regardless of original randomization. These patients will be included in the prevalence estimate, but excluded from the analysis of the treatment effects. An overview is provided in Fig. 1.

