### Study outcomes

Primary outcomes are 1) the prevalence of different sleep disorders as a function of individuals’ mental disorders (depressive disorder, bipolar disorder, anxiety disorder, PTSD, AD(H)D, ASD, SSD or personality disorder), and 2) the effect of sleep interventions on sleep, severity of specific symptoms of mental disorders, general functioning, and quality of life. Secondary outcomes are 1) the effects of sleep interventions on objective outcome parameters, for example use of sleep/sedative medication, number of hospitalizations and length of stay and, 2) differences between genders in the prevalence of specific sleep disorders and sleep intervention effects.

First, we expect that the prevalence of most sleep disorders among individuals with mental disorders will exceed those in the general population. Second, concerning the adjusted sleep interventions, we expect that the treatment of sleep disorders, tailored to mental disorders, will improve sleep, recovery from mental disorder symptoms, and quality of life in most patients. We hypothesize that the effect of added sleep intervention(s) will be larger than the effect of TAU alone in the TAU-SI-T1 group.

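### The rule for participants missing both T1 and T2 makes no exception for hospitalisations, length of stay and medication use, so these outcomes may be estimated in a selected subset

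*Protocol article*

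**What the plan says.** The rules are in the protocol article under Data exploration/ missing data. They apply "If a participant stops participation halfway the study or if a specific questionnaire is missing at a specific time point". Three patterns follow.

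- **Only T2 missing:** "if the last data point (T2) is missing, the participant will be included in the analysis for the prevalence and in any analysis focussed on" the T0 to T1 comparison.
- **A complete questionnaire missing at T1, T2 present:** "T1 will be treated as a missing data point and imputed using multiple imputation".
- **Both missing:** "If a participant is missing both the T1 and T2 data point, this participant will only be included in the prevalence analysis".

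Under Study outcomes, the secondary outcomes include effects of the sleep interventions on "objective outcome parameters, for example use of sleep/sedative medication, number of hospitalizations and length of stay". The article gives neither a data source nor a separate missing-data rule for these. The analysis section describes the target broadly: "The effects of added sleep intervention in all participants with a sleep disorder will be assessed at six and twelve months". Data collection is set out under Procedure: "Participants will be asked to complete questionnaires prior to the intake procedure (T0), 6 (T1), and 12 (T2) months later".

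**The concern.** Returning a T1 or T2 form happens after randomisation. A rule that ties inclusion to it is hard to avoid for a self-report scale, because without the form there is no outcome. Admissions, days in hospital and prescribed medication are different: they can be known for someone who returned nothing. Applying the same rule to them discards outcomes that may be available and makes the analysed set depend on a response that illness may affect.

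The setting makes this worth settling. The trial is open (Design), and between T0 and T1 only the early arm receives sleep diagnostics and treatment (Procedure), so retention of ill participants could differ by arm. Most patients are described as having chronic or complex disorders (Study population). The Background notes that "the already high vulnerability for suicidal behavior in individuals with mental health problems is further increased in those with poor sleep". That remark says nothing about missing data, but it explains why admissions are of interest in this population.

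**Working it through.** No figure in the plan decides this point. The sample-size section gives no attrition rate, so the share missing both time points cannot be taken from the document. The check is a reading of the rules, followed by an illustration.

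**1. Does the rule reach the objective outcomes?** The T1-only rule is worded for a missing questionnaire. The both-missing rule is worded for the participant, who is then kept for prevalence alone, without exception. The objective outcomes are treatment effects, not prevalence. Followed literally, the rule removes the participant from them. That sits badly with the stated aim of assessing effects in all participants with a sleep disorder.

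**2. Who is caught?**

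| Pattern | Effect of the rules as worded |
|---|---|
| T1 and T2 present | in all analyses |
| only T1 missing | kept, T1 imputed |
| only T2 missing | prevalence and T0 to T1 comparisons; not the 12-month comparison |
| both missing | prevalence only |

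A long-stay inpatient who completes either T1 or T2 is not removed by the both-missing rule. A participant who dies after completing T1 stays in the T0 to T1 comparison. Death brings the both-missing rule into play only when T1 is missing as well. An admission in months 6 to 12 that leads to a missed T2 alone is lost from the 12-month comparison through the T2-only rule.

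**3. Illustration with the same retention pattern in both arms.** All inputs are assumptions. Let p be the true proportion admitted, a the share of admitted participants missing both time points, and b the same share among the others. Then

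analysed proportion = p(1 − a) / [p(1 − a) + (1 − p)(1 − b)].

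Take p = 10% and 20% in the two arms and b = 10%:

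| a | lower arm | higher arm | difference |
|---|---|---|---|
| 10% | 0.09/0.90 = 10.0% | 0.18/0.90 = 20.0% | 10.0 points |
| 30% | 0.07/0.88 = 8.0% | 0.14/0.86 = 16.3% | 8.3 points |
| 50% | 0.05/0.86 = 5.8% | 0.10/0.82 = 12.2% | 6.4 points |
| 80% | 0.02/0.83 = 2.4% | 0.04/0.76 = 5.3% | 2.9 points |

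When a = b there is no distortion. When a exceeds b equally in both arms, the difference shrinks but the odds ratio does not change. The true value is (0.20/0.80)/(0.10/0.90) = 2.25, and at a = 50% it is (0.10/0.72)/(0.05/0.81) = 2.25.

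**4. Illustration with retention that differs by arm.** Assume 14% admitted in both arms and 88% of the non-admitted returning T1 or T2. The non-admitted then contribute 0.86 × 0.88 = 0.7568.

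- 50% of admitted participants return a form: 0.07/(0.07 + 0.7568) = 8.5%.
- 70% of admitted participants return a form: 0.098/(0.098 + 0.7568) = 11.5%.

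With 50% in both arms, each shows 8.5% and the difference is zero. With 50% in controls and 70% in the early arm, a 3.0-point excess appears in the early arm although there is no true effect. Swapping the two figures moves the same excess to the control arm. The sign is therefore set entirely by the assumption.

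**The case against.** The best reply is that the rules were meant for questionnaires. The section opens by announcing a separate analysis for each questionnaire, a missing questionnaire is one of the two triggers, and the models are fitted separately by outcome. On that reading, someone whose admissions are known is not missing that data point, and nothing is lost. The objective outcomes are also named only as examples, and an article may leave their source to a fuller document.

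This has weight: application to the objective outcomes follows from the wording and is not stated outright. It does not remove the point. The other trigger is stopping participation, and the consequence attaches to the participant, not to a scale. If only questionnaires were meant, the sentence says more than was intended and needs the same correction. The issue is the scope of a rule the article does state; the absence of a data source is not itself the fault.

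The reply also rightly blocks several stronger readings that a reader might infer:

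- **That long-stay patients, or those who die, drop out of these outcomes.** Nothing in the article links admission to missing both time points. Data are collected on the institute's own routine platform, so inpatients are not shown to be harder to reach. For schizophrenia spectrum disorder, T2 also includes an interviewer-rated PANSS.
- **That event rates are certainly understated in both arms.** This requires admitted participants to miss both time points more often than others.
- **That these are the only outcomes able to show serious harm.** They are secondary effect outcomes, and the symptom and functioning scales can also show worsening.
- **That controls go without care for six months.** Treatment as usual continues, and very severe sleep disorders are referred at once.

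**Conclusion.** The point holds as a fault in the scope of a stated rule. As worded, missing both T1 and T2 removes a randomised participant from the comparisons of hospitalisations, length of stay and medication use, although these need not depend on a questionnaire. Two conditions must be met for harm to follow: the data can be obtained without questionnaires, and missing both time points is related to admission or illness. The first is an inference from recruitment at a single institute; the second is plausible but unstated.

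The size and direction of any bias are unknown. Under the assumed figures, a true 10-point difference could shrink to between 8.3 and 2.9 points, and retention that differs by arm could create a spurious difference of about 3 points in either direction. If missingness is unrelated to admission, there is no distortion. The document does not support a claim that the bias runs against either arm. Only secondary outcomes are affected, but the rule is worth correcting because the remedy is small.

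**What to change.** In Data exploration/ missing data, state that the rules for missing T1 and T2 apply to questionnaire outcomes only. Then add, in substance:

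*Number of hospitalisations, length of stay and use of sleep or sedative medication are analysed in the assigned arm for all randomised participants whose data can be obtained without questionnaires (for example from the institute's care records, where consent covers this), whether or not T1 or T2 was returned. Follow-up ends at 12 months, or earlier at death or withdrawal of consent. Results for T0 to T1 are shown separately.*

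The separate display matters because T0 to T1 is the only period in which the arms differ in access to the sleep intervention. Since follow-up will differ in length, the analysis of counts and days should account for time observed. Deaths need not become a new outcome for this purpose; only their handling has to be stated.

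The change leaves the article's other exclusions untouched (immediate referral of very severe cases, an HSDQ score below the cut-off at T1, a diagnosis not confirmed). They are a separate matter.

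The cost is a small record extraction for participants without questionnaires and a check that consent covers record use. If it does not, the extra data may be unobtainable for some participants who have stopped responding, and their number per arm should be reported. No additional visits or participants are needed.
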